### Work package 5: equity assessment

In the light of concerns over health inequalities and ethnically disproportionate policing (Shiner et al., 2018), we will carry out an assessment of the equity aspects of our focus PDD schemes. This work package will draw on data collected for work packages two and three, and so will have the same participants. Quantitatively, we will test the hypotheses that there are significant differences in the proportion of eligible suspects that are offered diversion away from criminalisation by gender and ethnicity. We will also test the hypotheses that there are similar differences among suspects who are offered diversion in terms of: attending diversion; completing it successfully; and ending up with OOCDs or criminal sanctions for suspected offences. This will enable us to assess whether PDD leads to ‘net-widening’ and ‘mesh-thinning’ in these areas. These two phenomena, originally identified by Cohen (1979), refer to processes whereby purported alternatives to criminalisation can actually bring more people into the net of penal control and increase the obligations placed upon them. Given the known disproportionality of drug law enforcement in England and Wales (Shiner et al., 2018; Stevens, 2011), it is possible that these processes have more of an impact on people who are racialised as Black. We will seek to examine this possibility in both the aggregate data, and in the individual-level data collected for Work Package 3, although we are not yet certain that the individual-level data will include information on ethnicity to do so.

Using the qualitative data collected for the second work package, we will also look for any differences in the processes and reported outcomes of PDD schemes for people with other protected and PROGRESS + characteristics (O’Neill et al., 2014). These include place of residence, race/ethnicity, occupation/class, gender/sex, religion, education, socio-economic status, social capital, age, disability, time-dependent characteristics (e.g. educational transitions, leaving home), and relevant personal circumstances (e.g. previous experiences of local authority care and contact with the criminal justice system).

We have included questions in our schedules for interviews and focus groups and codes in our provisional coding framework that will elicit information on these potential axes of disparity and discrimination. In our qualitative analysis, we will run queries that search for data on these issues. This will enable us to provide distinct qualitative data that supplements the quantitative analysis of equity. Unfortunately, the quantitative datasets to which we will have access do not provide data on the full range of PROGRESS + characteristics.

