We will focus on the process, outcomes, cost consequences, and equity effects of PDD schemes in Durham, Thames Valley and the West Midlands. Our process evaluation will include a specific focus on the experiences of drug-involved suspects who are exposed to PDD schemes, whether they take up the diversion opportunities or not, as well as the police officers/staff and partner agencies who implement PDD schemes. In assessing outcomes, we will use data already collected by the police, NHS, and drug treatment services to assess the impacts of PDD on crime, hospitalisations and engagement with drug treatment. We will also examine how equitable the effects of PDD are (e.g. by ethnicity and gender). We will use existing realist frameworks such as EMMIE (Johnson et al., 2015), VICTORE (Cooper et al., 2020), and Carroll et al.’s (2007) conceptual framework for implementation fidelity. EMMIE highlights the Effect, Mechanisms, Moderators, Implementation and Economics of particular interventions or families of programmes (Johnson et al., 2015). VICTORE is a complementary but more detailed, realist framework which sensitises us to examine Volition, Implementation, Contexts, Time, Outcomes, Rivalry and Emergence (Cooper et al., 2020). Carroll et al’s (2007) framework is also complementary. It includes examination of four aspects each of adherence to the plans for the intervention (content, coverage, frequency, duration) and moderators of fidelity (intervention complexity, facilitation strategies, quality of delivery, participant responsiveness), plus the identification of essential components of the intervention.

Our analysis is split into six work packages which will produce a realist synthesis (Jagosh, 2019; Pawson, 2002) and a final, revised programme theory by the end of the project in spring 2025. In the remainder of this protocol, we report on the setting and content of the evaluated PDD schemes, and the methods adopted for each of the work packages of our evaluation. In creating this protocol, we have used the items of the RAMESES II reporting standards for realist evaluation (Welch & Tricco, 2016; Wong et al., 2016), although we have made some changes to their order (e.g. the programme theory appears in the section on work package 1) and we report methods separately for each work package. We will also use these standards for reporting results, including main findings, and consideration of strengths, weaknesses and future directions.

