Research participants who are drug-involved suspects will include: service users who were eligible for diversion, have been diverted, and are fully or partially participating in PDD schemes; and people who were eligible for diversion but were not diverted or are not participating. Interviews with drug-involved suspects will be carried out by User Voice’s peer researchers. Interviewees will be selected purposively to inform us on a range of experiences, according to gender, ethnicity, age, type of drug use (e.g. infrequent/frequent cannabis use, infrequent/frequent cocaine use, dependent use of heroin), and engagement in the diversion scheme (none/partial/full).

We will also gather aggregate police force level data for our three focus areas on the numbers of people who: are contacted as drug-involved suspects; are diverted to PDD schemes; participate in such schemes; complete the scheme; receive an OOCD; or receive some form of criminal justice sanction (e.g. caution, charge, sentence). We will ask for these data to be provided for each year from three years before the start of each PDD scheme to March 2024, and broken down by age group, gender and ethnicity. This will inform our analysis of implementation fidelity, as well as our equity assessment in work package 5.

Interviews and focus groups will be transcribed and anonymised and imported into Nvivo software for computer-assisted qualitative data analysis (Dalkin et al., 2021). We will also include memos on our descriptive analysis of the aggregate data in the qualitative dataset. Following adaptive theory (Layder, 1998), provisional codes for the analysis have been derived from our refined theory of change (see Fig. 1) and the conceptual frameworks we drew from EMMIE (Johnson et al., 2015), VICTORE (Cooper et al., 2020) and Carroll et al. (2007). Through a hybrid process of deductive and inductive reasoning and close reading of interview and focus group transcripts, as well as ‘attached memos’ (Dalkin et al., 2021), we will develop a final set of core and satellite thematic codes. These will form the basis for writing up findings on the contexts, mechanisms, moderators and outcomes of the three PDD schemes, and our analysis of the fidelity of implementation.

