We plan to use multivariable regression to estimate the effect of PDD on primary and secondary outcomes. Our analysis will control for potential confounders including age, sex/gender, ethnicity, health, previous experience of drug or alcohol treatment, offending history, reason for police contact, date of cohort entry, and the force-level baseline probability of each outcome. Our primary outcomes are count variables, and we will therefore use a mixed negative binomial model offset by the logged duration between the study entry date and the end of follow-up. We plan to use a negative binomial model rather than a Poisson model because we anticipate that both outcomes will be overdispersed, with some participants having high counts.

In our primary analysis, we will compare outcomes for all drug-involved suspects eligible for diversion in our focus areas (regardless of whether they were offered or took up diversion) with those for similar suspects in control areas. This is akin to an ‘intention to treat’ design in an experimental study (Hernán & Robins, 2016).

In our secondary analyses, we will:

Compare outcomes for participants who are diverted with those who are not. This is comparable to a ‘per protocol’ analysis in experimental trials (Hernán & Robins, 2016);Report access to diversion by age, sex, ethnicity, and socioeconomic status (as a complement to work package 5 on equity of effects).Test whether the effectiveness of diversion for each outcome varies by police force (while acknowledging that this analysis will have lower statistical power).

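### No stated quantitative analysis addresses equity of PDD's effects by gender or ethnicity, and net-widening is credited to tests that cannot show it

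*Protocol article*

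**What the plan says.** **The promise.** The Background says: "We will also examine how equitable the effects of PDD are (e.g. by ethnicity and gender". The section on the evaluated schemes repeats that equity of both implementation and effects will be analysed. Work package 6 equates effect with outcomes and draws it from Work packages 3 and 5.

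**The stated tests.** Work package 5 first tests "differences in the proportion of eligible suspects that are offered diversion away from criminalisation by gender and ethnicity". It then tests for "similar differences among suspects who are offered diversion in terms of" the following: "attending diversion; completing it successfully; and ending up with OOCDs or criminal sanctions for suspected offences".

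**Work package 3.** Sex/gender and ethnicity are adjustment variables in the outcome models. A secondary analysis reports access to diversion by age, sex, ethnicity and socioeconomic status, described "as a complement to work package 5 on equity of effects". The one test of whether effectiveness varies is by police force.

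**The inference on net-widening.** Straight after its hypotheses, Work package 5 says "This will enable us to assess whether PDD leads to" net-widening and mesh-thinning. It describes these as processes by which alternatives to criminalisation "can actually bring more people into the net of penal control and increase the obligations placed upon them".

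**The aggregate counts.** Work package 2 says "We will also gather aggregate police force level data for our three focus areas on the numbers of people" contacted, diverted, participating, completing, given an out-of-court disposal (OOCD) or sanctioned. They are yearly, start three years before each scheme, run to March 2024, and are split by age group, gender and ethnicity. They are said to inform Work package 5.

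**The concern.** Two stated questions do not match the analyses offered for them.

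First, equity of effects asks whether PDD changes hospital episodes or reoffending differently for women and men, or across ethnic groups. That needs the PDD-versus-comparison contrast within each group. The Work package 5 hypotheses concern how suspects move through the scheme and how the index case is disposed of. Equal access and completion could be reported as equitable effects when effects were never compared.

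Second, net-widening as the article describes it is about how many people are brought in. A proportion among people already eligible or already offered does not carry that information. A null result on the stated tests could be read as evidence against net-widening.

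In addition, comparing OOCDs and sanctions only among people offered diversion leaves out everyone who was not offered it. If one group is offered diversion less often and is sanctioned instead, the offered-only comparison misses it.

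The article expects its results to inform spending cases and national policing guidance, so what the equity analysis can support matters.

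**Working it through.** The article gives no sample size, power or significance level for Work packages 3 or 5, so there is no figure to reproduce. The check sets each stated test against the quantity it is meant to address.

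**Step 1. Tests against targets**

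| Stated analysis | Denominator | Outcome | Health or reoffending effect by group? | Change in numbers drawn in? |
|---|---|---|---|---|
| Work package 5, first hypothesis | Eligible suspects | Offered diversion | No | No |
| Work package 5, further hypotheses | Offered suspects | Attendance, completion, OOCD or sanction | No | No |
| Work package 3, access report | Not stated | Access to diversion | No | No |
| Work package 3, effect variation | Full cohort | Each outcome, by force | No, by force only | No |
| Work package 2 counts | Yearly totals, PDD forces | Contacted, diverted, OOCD, sanctioned | No | Yes, descriptively |

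**Step 2. Can the conditional tests see net-widening?** All counts here are assumed for illustration; none comes from the article. Take pre-scheme contacts of 1000 in group A and 500 in group B. After launch, in both groups, 60% of eligible suspects are offered diversion, 80% of those offered attend, and 30% of those offered receive an OOCD or sanction. Everyone contacted is treated as eligible.

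| Scenario | Contacts A / B | Offered | Attend | OOCD or sanction | Post/pre contacts A / B |
|---|---|---|---|---|---|
| No widening | 1000 / 500 | 600 / 300 | 480 / 240 | 180 / 90 | 1.0 / 1.0 |
| Both groups up 50% | 1500 / 750 | 900 / 450 | 720 / 360 | 270 / 135 | 1.5 / 1.5 |
| Group B doubled | 1000 / 1000 | 600 / 600 | 480 / 480 | 180 / 180 | 1.0 / 2.0 |

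In all three scenarios the conditional proportions are 0.60, 0.80 and 0.30 in each group, and the chi-square p value comparing A with B is 1.0 for offer, attendance and disposal alike. Completion among those offered has the same structure. Only the post/pre ratio of contacts separates the scenarios, and that is what the Work package 2 series supplies.

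**Step 3. Can they see unequal effects?** Suppose the PDD-versus-comparison rate ratio for reoffending is 0.8 in A and 1.2 in B, again assumed. The ratio of rate ratios is 1.2 / 0.8 = 1.5, with effects in opposite directions. Every Work package 5 process proportion is unchanged, because no follow-up outcome enters any of them.

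**Step 4. The offered-only disposal comparison.** Let o be the proportion offered among eligible suspects, s the sanction proportion among those offered, and u that among eligible suspects not offered. The overall sanction proportion is o·s + (1 − o)·u. If s and u are equal in A and B but o differs, the overall difference is (o_A − o_B)(s − u), while the offered-only comparison gives s − s = 0. The first hypothesis would detect o_A ≠ o_B, but no stated hypothesis test shows what that does to sanctions.

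**The case against.** The strongest reply concerns net-widening. A reader might infer that the protocol has no quantitative route to it, and the article does not support that. The Work package 2 counts include people contacted, have a three-year pre-scheme baseline, are split by gender and ethnicity, and feed Work package 5. That section also says the possibility of a greater impact on people racialised as Black will be examined in aggregate and individual-level data. This stands: a descriptive route exists. What remains is that the text attaches the net-widening inference to the conditional tests, that the series covers only the PDD forces, and that no comparator allows for secular trend.

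The offered-only point is partly met, since the first hypothesis tests who is offered diversion and the aggregate counts allow sanctions to be described relative to people contacted. It survives only as a choice of denominator in the stated disposal hypothesis.

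The article also condenses a fuller plan, and interaction terms are often left to the analysis plan. But it is not silent here: it names hypotheses, denominators and endpoints, and says what they will enable. Work package 5 does look for differences in reported outcomes, but qualitatively. Nor does Work package 3 hand effects over to Work package 5; it calls its access report a complement to that work.

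A reader might further infer that undetected net-widening biases the primary rate ratio towards benefit by a calculable amount. The article gives no figure for extra contacts or their risk. The outcome models also adjust for offending history, health, previous treatment, reason for contact and force-level baseline probability, which could absorb an unknown share of any such shift. No size can be put on it.

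**Conclusion.** The point holds in two limited parts.

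- **Equity of effects.** The aim is promised, but no stated quantitative analysis compares health or reoffending effects by gender or ethnicity. This follows from the text alone and depends on no assumed figure.
- **Net-widening.** The tests to which it is credited cannot show it, whatever their result. The pre/post counts elsewhere in the article can, but only descriptively and without a comparator. The assumed counts above illustrate this; the conclusion follows from the denominators.

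The disposal comparison among offered suspects is a lesser point: it describes one stage and should not be the only test of disparity in sanctions.

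These are secondary analyses and the primary comparison is untouched. The change should be made before results are seen, because choosing the groups for effect tests afterwards would weaken any equity claim. The article itself discloses that individual-level ethnicity may not be available, so the ethnicity part of the remedy is conditional. The gender part does not depend on that.

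**What to change.** 1. **Effects by group.** Add a PDD-by-gender interaction to both primary outcome models, and a PDD-by-ethnicity interaction if individual-level ethnicity is obtained. Report subgroup rate ratios with intervals, labelled secondary and likely imprecise. If ethnicity is not obtained, say that equity of effects by ethnicity cannot be assessed quantitatively. Cost: analysis time, and estimates that may be too imprecise to settle the question.
2. **Disposal.** Analyse OOCD or sanction by gender and ethnicity with all eligible suspects as the denominator, and keep the offered-only comparison as description. Cost: a change of denominator, subject to the same limit on individual-level ethnicity.
3. **Net-widening.** Base the assessment on the pre/post contact and sanction counts from Work package 2, overall and by gender and ethnicity, and reword Work package 5 accordingly. Where obtainable, request the same yearly counts from the three comparison forces to allow for secular trend. Cost: one further aggregate request, to forces now asked only to identify individuals from a one-year window. If the counts cannot be had, state that the before-after change is uncontrolled.

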### Work package 6: realist synthesis

In this final work package, we will bring together all our findings in the form of a realist synthesis of what works, for whom, in what circumstances and why. To do this we will employ the EMMIE and VICTORE framework (Cooper et al., 2020; Johnson et al., 2015). Taken together, the work packages provide detail on all the components of these framework.

Effect is synonymous with outcomes and so data from work packages 3 (quantitative outcome assessment) and 5 (equity assessment) will be used here. The Mechanisms, Moderators and Implementation are central to the delivery of the process evaluation in work package 2. Work package 4 will detail the economics of PDD in the form of the CCA. Our analysis in work package 2 also employs the VICTORE framework to sensitise us to issues of Volition (the intentions and choices of people involved in the PDD schemes), Time (including changes in implementation over time), Rivalry (the presence and effects of similar or competing interventions for the target group), and Emergence (the features of PDD schemes that arise from the combinations of other factors). Work packages 2 and 5 will provide detail on the implementation of PDD schemes. Work package 4 will detail the economics of PDD in the form of the CCA.

As realism encourages us to think beyond ‘what works’, in our synthesis we will unpack what it is about PDD that leads to the observed pattern of outcomes. In other words, we do not view exposure to PDD as an independent variable that can be experimentally closed off from all other factors (Deaton & Cartwright, 2018). We are interested in what it is about PDD schemes that produce outcomes in particular contexts. In this sense, the findings of the realist synthesis will enable us to refine further the programme theory in Fig. 1 and then use this as the platform for developing actionable guidance for the future rollout of PDD programmes.

## Dissemination

We have developed a dissemination plan to reflect the diverse needs and interests of the likely audiences for the PDD evaluation. These audiences are varied and consist of: (a) police and health partners (such as government departments, police forces, local authorities and service providers); (b) public stakeholders (e.g. criminal justice charities and advocacy groups); (c) service users; (d) academics and other researchers; and (e) the wider general public.

Dissemination of our research findings will be principally based around two types of publication. First, a series of academic journal articles covering different aspects of the PDD evaluation are to be submitted for publication. Separate articles are planned on the results of each of the work packages (i.e., the qualitative process evaluation, quantitative impact assessment, cost-consequence analysis, equity assessment, and realist synthesis). In addition, we will consider submitting articles on a range of thematic, theoretical and methodological issues (such as data linkage, policy learning, and research coproduction). The main audiences for this type of publication will be academics, researchers, and a range of partners and stakeholders. To ensure transparency and maximise the public use and social value of the research, we plan to make preprint and open access copies of these publications available via the Kent Academic Repository.

Second, the College of Policing, which is one of the partners in the project, will publish a summary of our evaluation findings. This summary may take the form of a single report covering the evaluation as a whole or a series of reports, one for the results of each work package. The summary report(s) will be written in plain English for non-specialist audiences (such as the police, public and some stakeholders), and will be made publicly available under an open licence via the National Police Library. The College of Policing also plans to host links to all journal articles and plain-English summaries on its website.

In addition to these formal publications, we intend to disseminate the PDD evaluation findings via a range of more informal communication channels. These channels are likely to include: briefings to relevant government departments and agencies, and the media; the circulation of evaluation outputs through national and regional networks (such as the networks of the members of our project advisory group that extend across the UK civil service) and online knowledge sharing platforms (like the Police Knowledge Hub); conference presentations to policy, practitioner and academic audiences; local workshops with service users and practitioners; social media; and specialist and sector-specific publications.

Pathways to research impact on policy and practice are built into our dissemination plan by virtue of the evaluation being funded by the Cabinet Office, and the College of Policing and National Police Chiefs’ Council (NPCC) being collaboration partners. The Cabinet Office’s Evaluation Accelerator Fund that has financed the PDD evaluation was established for “the creation of actionable evidence in [Government] priority areas to inform decision-making at the next spending review” (HM Government, 2023). The reports we are required to submit to the Cabinet Office as part of the funding arrangement may, therefore, be used to support business cases to the Treasury for an increase in government spending on PDD (if the evaluation can demonstrate that PDD has a positive impact on outcomes and is cost-effective). Collaboration with the College of Policing and NPCC provides us with opportunities to influence policing policy and practice. The College of Policing—as the professional body for policing in England Wales—sets the standards for policing in the form of the national policing curriculum and operational guidance. The College of Policing has agreed to develop evidence-based guidelines on the implementation of PDD, subject to the evaluation showing that it had a positive impact on outcomes. The NPCC sets the strategic direction for policing and is responsible for coordinating policing activities across England & Wales, and, as such, will have an important role in supporting implementation of the College’s guidance.

